## Study File

All associated study correspondence will be filed by the Investigator and will be available for inspection by the Sponsor or designee to determine that all documentation is present. It will be responsibility of the Investigator to provide adequate means for organisation and filing of study documentation at the study centres.

## Initiation of the Study

Prior to the commencement of the study, designated representatives from Starpharma and DAIDS will visit the investigational site to ensure adequacy of facilities and to discuss with the Investigator, and other personnel involved with the study, their responsibilities with regard to protocol adherence.

The investigational staff may not enrol any subjects prior to receipt of written approval from the IEC by Starpharma, and completion of a formal meeting conducted by the Starpharma representative to initiate the study. This meeting will include an inventory of study supplies and a detailed review of the Protocol and CRFs. In addition, study participants may not be enrolled until the site has been activated by DAIDS and written confirmation of this activation has been received by Starpharma.

## Subject Reimbursement

Subjects will be reimbursed according to the guidelines of the IEC/IRB in order to compensate them for their inconvenience and time.

## Subject Identification

All subjects screened for a study will be allocated a unique screening identifier and entered chronologically on the Subject Log at the initial visit. In the event that a subject is not included in the study, the reason is to be documented in the space provided on the Subject Log.

The eligible subjects entering the Study will be assigned a Subject Allocation/Randomisation Number in sequential order. The Subject Allocation/Randomisation Number will be entered on all pages of the CRF.

Although pre-study samples will be couriered directly from the study participant’s home, the courier will transport the sample concealed in an opaque bag, and be unaware of the nature of the sample (except that it is biological in nature and un-infected), the study for which it is used, and any of the subject details. The opaque bag will contain the participant and sample identification numbers, will be sealed and tamper evident to prevent inspection by the courier.

## Confidential Follow-up

The investigator will be responsible for retaining sufficient information about each subject (e.g. name, address, phone number, and identity in the study) so that regulatory agencies or Starpharma may access this information should the need to do so arise. These records should be retained in a confidential manner, as legally mandated according to local requirements, and stored separately from all other study documentation.

## Recording of Data

The investigator should maintain the individual subject files separate to the CRFs. The files should include visit dates of the subject, records of vital signs, medical history or examinations administered, laboratory results, concomitant treatments. Any AE encountered and other notes as appropriate. This constitutes ‘source data’. All entries on the CRFs must be backed up by source data, unless agreed that the CRF will constitute source data.

The CRFs must be kept in order and up-to-date so that they always reflect the latest observations on the subjects enrolled in the study.

Each subject’s file should have attached to it the original signed Informed Consent. When the study treatment is completed, the Informed Consent should be kept on file with a copy of the completed CRF in the appropriate file folder provided, or a note made indicating where the records can be located. All records should be kept in conformance with applicable national laws and regulations.

All original laboratory reports should be available for review in each subject’s file. It is important that the original reports are available for review because of the possibility of inaccuracies or errors in transcribing data from original records to the CRF.

CRFs must be completed legibly for each subject enrolled in the study and signed-off by the investigator. This should be done as soon as possible after completion of therapy.

## Monitoring of the Study

The investigator will permit Starpharma and its agents to monitor the study as frequently as Starpharma deems necessary to determine that data recording and protocol adherence are satisfactory. An independent Study Monitor will collect CRFs and to verify subject data on the CRFs for analysis.

The investigator will allow Starpharma and its agents reasonable access to the CRF and related source documents for monitoring purposes as frequently as Starpharma deems necessary. This includes tests performed as a requirement of participation in this study and may also include other medical records required to confirm information contained in the CRF such as past history and secondary diagnoses.

At each subject visit, the investigator or delegate should record all data generated since the last visit on the CRF. The investigator and his/her staff will be expected to co-operate with the monitor to assist in providing any missing information.

The Study Monitor will require access to the Investigator’s study file to ensure completeness of all study-related documentation. The Study Monitor will provide the investigator with adequate means for organization and filing of study documentation at the study centre.

The date the Study Monitor visits the investigational site will be recorded in the site visit log. During monitoring visits, the study site co-ordinator and investigator should be available, the source documentation will be accessible and a suitable environment will be provided for the Study Monitor to review study related documentation.

The key purposes for monitoring visits by the Study Monitor include the following:

- 1. Helping to resolve any problems.
  2. Examining all study documentation for completion, adherence to the protocol and possible adverse events.
  3. Discussing inconsistencies or missing data.
  4. Ensuring all study materials are correctly stored and dispensed.
  5. Verification of study data with source documents.
  6. Checking fulfilment of the obligations of the Investigator.
  7. Reviewing consent forms and date of consent.
  8. Inspecting study drug (storage, labelling and documentation).

The investigator will provide Starpharma with the completed and signed CRFs at the end of the study period planned for each subject within 4 weeks of the last subject completing the study.

## Protocol Deviations

Study subjects who are found not to have complied with the requirements of the protocol must be reported to Starpharma, and subsequently by Starpharma to the DAIDS Medical Officer. Such subjects may be withdrawn from the study or statistical analyses at the discretion of the Investigator/Starpharma.

Deviations from the protocol should not be made other than as part of a protocol amendment agreed with Starpharma and DAIDS, except where necessary to eliminate an immediate hazard to study subjects. If a protocol deviation occurs, the Investigator must notify Starpharma and the appropriate IEC/IRB as soon as possible. Starpharma must notify the DAIDS Medical Officer.

Evaluability of such subjects for analysis will be decided through discussion between Starpharma, the study statistician, the investigator and the DAIDS Medical Officer at the end of the study. All protocol deviations must be noted and explained in the Investigator’s file.

Protocol deviations can be divided into two categories as follows:

Minor Protocol Deviations

- - all instances where the protocol specified instructions have not been followed during the on-study period. For example, a subject does not provide a blood sample as required or a visit occurs outside the acceptable window period.

Major Protocol Deviations (also known as “Protocol Violations”)

- - when the subject did not meet all inclusion and/or exclusion criteria prior to entry into the study;
  - if additional blood samples are taken or other procedures performed that are not specified in the protocol.

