## Method of Subject Assignment

This is an open-label study. Study participants will be allocated a unique participant identification number at randomization in sequential order.

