## Treatment Allocation and Randomisation

Participants will be randomly allocated to one of the following study groups. Their sampling sequence is determined by the group to which they are randomised.

|  | **Treatment Period 1** | **Treatment Period 2** | **Treatment Period 3** | **Treatment Period 4** | **Treatment Period 5** |
| --- | --- | --- | --- | --- | --- |
| **Group A** | 0 h | 1 h | 3 h | 12 h | 24 h |
| **Group B** | 1 h | 3 h | 12 h | 24 h | 0 h |
| **Group C** | 3 h | 12 h | 24 h | 0 h | 1 h |
| **Group D** | 12 h | 24 h | 0 h | 1 h | 3 h |
| **Group E** | 24 h | 0 h | 1 h | 3 h | 12 h |

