## Pharmacokinetic Assay

CV samples will be assayed for SPL7013 levels using a validated capillary electrophoresis bioanalytical method at the Starpharma Pty Ltd bioanalytical laboratory, Melbourne, Australia.

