## Confidentiality

Members of the study staff sites are all trained in subject confidentiality. The log of study participant names and other protected health information will be kept in a double-locked area. All computer information about study volunteers will be kept on a computer with log-on passwords. Laboratory specimens are labelled with study numbers and date, and are delivered or shipped by study staff. The study sites’ data management and clinical staff are the only personnel with access to the protected health information of study volunteer. Each member of the staff has a log-on identification and password, logs off before leaving a computer screen unattended, and closes their office door when out of the office. All research records will be kept indefinitely following closure of the study.

Starpharma will preserve the confidentiality of subjects taking part in this study. In the event of names inadvertently appearing on study documentation, this information will not be processed.

Subject medical records pertaining to this study may be inspected/audited at any time by Starpharma employees or their duly authorised representatives, a regulatory authority or the IEC/IRB. All records accessed will be strictly confidential. Consent to participate in this study includes consent to these inspections/audits.

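### Section 12.9 allows non-compliant women to be dropped from the analyses at discretion, beyond the Per Protocol rule and with no requirement that assay results be unseen

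*Protocol*

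**What the plan says.** Section 12.9 (Protocol Deviations) holds two rules for women who have not followed the protocol. The first gives discretion to two parties: "Such subjects may be withdrawn from the study or statistical analyses at the discretion of the Investigator/Starpharma". The second has evaluability decided in discussion between the sponsor, "the study statistician, the investigator and the DAIDS Medical Officer at the end of the study".

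Section 10.2.2.2 defines the Per Protocol set by a fixed rule: randomised, at least two completed periods including the 0 h sample, and no major violation. Section 10.2.3.1 makes this the only set for the primary endpoints. Section 12.9 limits major violations to eligibility failures and to extra blood samples or procedures outside the protocol. Any other failure to follow instructions is minor, and a visit outside its window is one of the examples given.

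On masking, Section 5.3 states "This is an open-label study". What is randomised is the order of the sampling times (Section 6.4: "Their sampling sequence is determined by the group to which they are randomised"). Drug levels are measured with a "validated capillary electrophoresis bioanalytical method at the Starpharma Pty Ltd bioanalytical laboratory" (Section 7.2.3). Section 11.5 adds that "Laboratory specimens are labelled with study numbers and date". No section describes masking of assay staff to sampling time.

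**The concern.** One section names two different sets of decision-makers for the same question, and both have wider grounds for exclusion than the analysis-set definition. A woman whom Section 10.2.2.2 keeps can be removed under Section 12.9 for a minor deviation, and the people deciding may already know her results.

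The study is meant to guide how long before intercourse the gel should be applied (Section 2.2) and to supply a variability estimate for powering later studies (Section 10.4). With 12 women, leaving out one whose activity fell sharply makes retention look longer and the spread look smaller. Leaving out one with little decline does the reverse to retention.

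**Working it through.** **1. The three rules side by side**

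| Rule | Who decides | Grounds | Timing against assay results |
| --- | --- | --- | --- |
| 12.9, discretionary sentence | Investigator or sponsor | Any non-compliance | Not stated |
| 12.9, evaluability sentence | Sponsor, statistician, investigator, DAIDS Medical Officer | Any non-compliance | End of study; results may be known |
| 10.2.2.2 with 10.2.3.1 | Fixed rule | Major violation, fewer than two periods, or no 0 h sample | Can be applied without results |

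Test case: a woman gives all five samples but attends one visit outside its window. Section 12.9 calls that minor, so Section 10.2.2.2 keeps her. Either sentence of Section 12.9 can still take her out. The rules give different answers for the same woman.

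**2. Does anything else keep results away from the deciders?** Section 10.7 rules out interim analyses but does not delay knowledge of assay values. Section 12.10 provides for procedures and audit, not for withholding results. The sponsor is one of the deciders, and its own laboratory measures concentration, from which mass is calculated. Those are two of the four primary endpoints in Section 10.1.1.

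**3. Size.** Section 10.3 gives no power, effect or SD, so there is no stated figure to reproduce. What follows is an illustration.

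Inputs from the protocol: n = 12 (Section 5.2); paired t-test of each time point against 0 h (Section 10.4). Assumptions: two-sided 5% level, normal differences, and a true decline of 0.889 SD. That decline was chosen because it gives 80% power at n = 12 from the noncentral t distribution with 11 degrees of freedom and noncentrality 0.889 × √12 = 3.08. In 200,000 simulated trials the women with the largest decline were removed:

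| Women removed | Mean decline (SD) | Chance of a significant decrease | Same number lost at random |
| --- | --- | --- | --- |
| 0 | 0.89 | 80% | – |
| 1 | 0.74 | 69% | 76% |
| 2 | 0.62 | 56% | 71% |
| 3 | 0.50 | 43% | not computed |

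Check by algebra: removing one of 12 moves the mean by her distance from it divided by 11. The simulated shift of 0.889 − 0.742 = 0.147 SD therefore implies that she lay about 0.147 × 11 = 1.62 SD from the mean.

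Effect on the spread: for a woman z sample SDs from the mean, the variance after removal is (11 − 12z²/11)/10 of its former value. At z = 1.62 this is (11 − 2.86)/10 = 0.81, so the SD falls to √0.81 = 0.90 of its value. A later study sized for the same difference would come out about 19% smaller, because sample size is proportional to variance.

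**4. Labels.** The five sequences in Section 6.4 are rotations of one cycle, and dates put a woman's samples in order. If the hour of one sample is known, the other four follow. The label described in Section 11.5 does not itself give any hour.

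**The case against.** Fixing analysis sets before results are released is usually SAP or data-review material, and the SAP is not shown. That would answer a complaint about silence. It does not answer a written discretion that contradicts the analysis-set definition in the same protocol.

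Several stronger readings are tempting, and the document does not support them:

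- **That the laboratories hold the allocation.** No section gives it to them. The protocol is silent on masking, and sample handling is left to procedures not shown. Step 4 needs one hour to be known first.
- **That sponsor and investigator alone settle evaluability.** The statistician and the DAIDS Medical Officer share that decision. Only the discretionary sentence leaves them out. Deviations must also be reported to DAIDS and the ethics committee.
- **That single samples, or any woman, can be dropped.** Section 12.9 concerns subjects, and only those found non-compliant.
- **That exclusions will be made with results in view.** This is permitted, not planned.
- **That outliers can be discarded.** Section 10.4 responds to outliers by changing to a rank-based test, not by removing the woman.

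It is also fair that every dose is the same gel, that the read-outs are largely instrumental, that the laboratory producing primary endpoint data is audited, and that use of the sponsor's laboratory is disclosed. These points make masking of assay staff an improvement rather than the correction of an error. They do not touch the exclusion rule.

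The figures in step 3 are a worst case, since they suppose that the women with the largest decline are also the non-compliant ones. The study looks for a gross drop (Section 2.3), which a shift of 0.15 SD would not hide.

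**Conclusion.** The point holds for the exclusion rule. Section 12.9 contradicts itself on who decides and goes beyond Section 10.2.2.2 on the grounds. It leaves open that exclusions from the only primary analysis set are made with results known. The conflict follows from the text alone and rests on no assumption.

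Its numerical effect cannot be derived from the protocol. Under the assumptions stated, targeted removal of one or two of 12 women lowers the chance of a significant decrease by 11 to 24 percentage points (80% to 69% or 56%). Of that, 4 to 9 points would be lost by random removal of as many women (80% to 76% or 71%). The correction is worth making because the result feeds dosing-time guidance and later sample sizes, and because it costs almost nothing. The lack of specified laboratory masking is secondary.

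**What to change.** **Main change, Section 12.9**

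1. Delete the words *or statistical analyses* from the discretionary sentence. Leave withdrawal from the study as it stands.
2. State that exclusion from the primary analysis follows Section 10.2.2.2 only. A woman withdrawn after two periods including 0 h, with no major violation, then stays in the set.
3. Have the four named parties decide and sign evaluability from clinical and deviation records before any assay result is released to them. Every criterion in Section 10.2.2.2 can be judged from those records. Because the sponsor's laboratory runs the concentration assay, the sponsor's deciders must be kept apart from its assay output until sign-off.

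The cost is an edit to one section and a change in the order of two end-of-study steps.

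**Secondary improvement.** Send processed aliquots to the assay laboratories under random codes without subject number, date or time point. Link sample weights through the code, since mass depends on them. The cost is a code list, someone to hold it and some relabelling. A 0 h sample may remain recognisable, so the protection is partial.

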## Data Quality Control

Throughout the Study, the data will be monitored and the CRFs checked against the subject’s medical record for completeness and accuracy. This will be performed by the Study Monitor.

Following completion and collection of the CRFs, the data will be checked manually, entered into a database and electronically checked for consistency and range. Queries will be generated for spurious data and clarification sought from the responsible Investigator or delegate at the Study site.

These data queries must be resolved in a timely manner by the Study site.

All laboratory assays will be conducted according to the protocol as laid out in the Study Procedures Manual and standard laboratory-specific SOPs. The laboratory responsible for generation of primary endpoint data will be subject to audit during the course of the study to ensure compliance with these procedures.

## Quality Assurance Audit/Inspection

The Study may be subject to an audit by an authorised representative of Starpharma and/or an authorised Regulatory Authority (e.g. TGA, FDA).

Regulatory authorities may request access to all study documentation, including source documents for inspection and copying, in keeping with local regulations. Starpharma will immediately notify the Investigator of an upcoming audit/inspection.

In the event of an audit, all pertinent study-related documentation must be made available.

If an audit or inspection occurs, the Investigator will permit the auditor/inspector direct access to all relevant documents and allocate his/her time as well as the time of relevant staff to discuss the findings and any relevant issues.

## Study and Site Closure

Starpharma reserves the right to prematurely discontinue or suspend the study either at a particular site or at all sites at any time and for any reason. If such action is taken, a Starpharma Clinical Representative will discuss this with the Investigator at that time and notify the Investigator in writing. If the study is suspended or terminated for safety reasons the Investigator conducting the study will be immediately notified of the action as well as the reason for it, as will the relevant regulatory agencies. The Investigator will advise the IEC/IRB overseeing the study at their site.

Upon closure of the study (whether at the expected conclusion or prematurely), the following activities will be checked by the Starpharma Clinical Representative, and the Principal Investigator will be notified of any discrepancies for investigation, correction and/or explanation:

1. Return of all study data
2. Data clarification and resolution of queries
3. Study product/drug accountability, reconciliation and final disposition
4. Review of site study records for completeness
5. Shipment of any relevant samples to the central laboratory

## Record Retention

All study documents, including the protocol and CRFs, are the confidential property of Starpharma and should be regarded as such. Unused CRFs must be returned to Starpharma or destroyed at the end of the study. Completed CRFs will be returned to Starpharma during the study by a method agreed by the study monitor. A study document binder will be provided by Starpharma for all required study documents. A checklist of all records to be retained by the Investigator will be provided by Starpharma.

Following completion of the study, the Investigator will retain copies of the approved protocol, completed CRFs, informed consent documents, relevant source documents, and all other supporting documentation related to the project in accordance with the applicable regulatory requirements. In Australia, documents must be retained for a minimum of 15 years from the date of termination of the study or for at least 2 years after the last approval of a marketing application in an ICH region, or at least 2 years after the formal discontinuation of the clinical development of an investigational product. Starpharma will confer with NIAID/DAIDS to assure that record retention is in accordance with current NIAID/DAIDS policies.

In the event that the Investigator retires or relocates, custody of the records may be transferred to another suitable person who will accept responsibility for the records. Notice of such transfer should be given to Starpharma Pty Limited in writing.

